**Table 3 Tab3:**
[figure not shown]
Schedule of enrolment, interventions, and assessments

*monthly average values of daily measurements collected by mobile application

### Statistical analysis

Statistical analysis will be performed using SPSS software. As stated in the method section, the system will be tested in two stages.

### Stage 1

For the first stage, the comments in the feedback forms will be used for revisions of program. Descriptive analyzes will be done for web site usability test results.

### Stage 2

At the end of the intervention, independent samples t-tests will be performed to measure the difference between the intervention and control groups. On both groups, one-sample t-test will be performed to measure the difference between baseline and post intervention in the same group.

Each of the dependent measures of primary outcomes will be analyzed using a generalized linear mixed model involving a single between Group factor (Treatment vs. Control), a single within Period factor (enrollment vs. end of 6 months), and interaction between Group and Period factor. Categorical data of both control and intervention groups will be analyzed together using logistic regression. The rates of controlled and uncontrolled diabetes patients will be determined.

An intention-to-treat analysis will be performed. The analysis will include all individuals’ data. In the analysis, patients will be compared regardless of patient compliance, crossover to other treatments, or withdrawal from the study.

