• Over age 40 • Volunteer • Computer and Internet literacy • DM diagnosed or having at least one of diagnostic criteria. These criteria; • HbA1c ≥ 6.5 • FPG ≥ 126 mg / dl • 2-h postprandial glucose ≥200 mg / dl • Any time postprandial glucose ≥200 mg / dl • Diabetes symptoms	• Having communication problems • Type 1 diabetes • MODY type DM • Psychotic disorders • Dementia

### Stage 2

In the second stage, the health data of 3000 participants will be evaluated to determine the effectiveness of CDSMS in screening. Participants who use medicine for DM treatment will be excluded from data analysis when measuring the effectiveness of the system in screening.

Patients who applied to primary health care services for any reason and screened within the scope of periodic health care for diabetes, having at least one measurement of FPG (Fasting Plasma Glucose), HbA1C or PPG (Postprandial Plasma Glucose) in last six months will be participants of stage 2. Participants determined in second phase will be evaluated in terms of inclusion and exclusion criteria. Eligible and volunteer participants will take part in the trial. Inclusion and exclusion criteria for randomized controlled trial are listed below in Table 1.

Patients who were diagnosed with DM among 3000 participants (new diagnosis, former diagnosis, medicine users, non-medicine users) will form the population of the randomized controlled trial. The sample size evaluated by significance level *p* = 0.05, 80% power, 25% prevalence (controlled diabetes) and odds ratio 2 will be included to experimental study. Because in RCT studies lost to follow up is approximately 15.0%, this amount is taken into account for determining the sample size. The sample contains 439 patients with 110 interventions and 329 control groups. The ratio of intervention to non-intervention (controls) is 1:3. About 3000 people over age 40 apply to the 10 primary health care units (In the city of Izmir in Turkey) in a month. For reaching expected number of samples, at least %14 of patients are thought to be eligible for inclusion criteria. (assuming DM prevalence approximately 14%).

Diabetes symptoms aforementioned in Table 1 are classical symptoms of polyuria, polydipsia, polyphagia or loss of appetite, weakness, fatigue, dry mouth, nocturia. Less common symptoms are blurred vision, unexplained weight loss, persistent infections, recurrent yeast infections and itching [10].

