### Measures

Primary outcomes of RCT include HbA1c, Fasting Blood Glucose and Postprandial Blood Glucose levels. Secondary outcomes include body mass index, diabetes-related emotional burden and interpersonal distress sub-scales, self-efficacy for diabetes self-care, blood glucose monitoring, physical activity, nutrition, medication-taking, diabetes self-care: blood glucose self-monitoring, medication-taking, smoking and alcohol using and physical activity, depression, anxiety, stress levels. Clinical and laboratory outcomes will be face-to-face assessed, others will be online self-assessed. The effectiveness of the system will be evaluated by using primary and secondary outcomes.

Table 2 lists all the outcomes and measures used in this study. Fasting blood glucose, HbA1c and other tests according to patient history and physical examination will be determined and implemented for each patient taken into intervention and control groups. Body mass index of patients will be calculated. On baseline all scales will be implemented online such as Diabetes Distress Scale [40], Diabetes Self-Efficacy Scale [41], Diabetes Self-Care Activities Survey [42], Morisky Medication Adherence Scale [43], The Patient Assessment of Chronic Illness Care-Patient Form [44, 45]. Monthly average of FPG and PPG values of patients regularly taken from the tele-monitoring system will be evaluated. Glycosylated hemoglobin (HbA1c) test will be done quarterly.

**Table 2 Tab2:** Measures

Measurement area	Outcomes assessed	Measure/s
Demographics	Age, gender, nationality, country of birth, relationship status, employment status, health insurance	Short answer and multiple choice items
Laboratory	Glycosylated hemoglobin A1c (HbA1c) level Fasting And Postprandial Blood Glucose	Venous blood sample
Clinical	Height, Weight, Diabetes Symptoms, Risk Factors	Patient history and physical examination
Emotional/ Psychological	Depression, anxiety, stress levels Diabetes-related emotional burden and interpersonal distress sub-scales Self-efficacy for diabetes self-care: blood glucose monitoring, physical activity, nutrition, medication-taking	Diabetes Distress Scale [40] Diabetes Self-Efficacy Scale [41]
Behavioral	Physical activity Diabetes self-care – blood glucose self-monitoring, medication-taking, smoking and alcohol using and physical activity	Diabetes Self-Care Activities Survey [42] Morisky Medication Adherence Scale [43]

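### Stage 2 lists overlapping analyses without saying which one decides; the within-arm tests have no control, and no stated analysis adjusts efficiently for baseline

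*Protocol article*

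**What the plan says.** The Protocol article, Statistical analysis, Stage 2, sets out three procedures for continuous data.

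- Between arms: "At the end of the intervention, independent samples t-tests will be performed to measure the difference between the intervention and control groups". No outcomes are named and no baseline term is mentioned.
- Within each arm: "On both groups, one-sample t-test will be performed to measure the difference between baseline and post intervention in the same group".
- For each primary outcome (HbA1c, fasting and postprandial glucose, per Measures), a generalized linear mixed model with a Group factor, "a single within Period factor (enrollment vs. end of 6 months), and interaction between Group and Period factor".

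Categorical data go to logistic regression. None of these is ranked above the others. The same section then states: "An intention-to-treat analysis will be performed. The analysis will include all individuals’ data".

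Elsewhere, Measures says that effectiveness is judged by comparing the two groups, that baseline tests are repeated at six months, and "Glycosylated hemoglobin (HbA1c) test will be done quarterly". Follow-up says that month 0 is compared with month 6. Participants and sample size gives 110 intervention and 329 control patients, with an allowance for about 15% loss.

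**The concern.** Three things looked wrong.

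1. A test of change inside one arm measures everything that happens over six months: time trend, usual care and, for patients who enter on a glucose threshold, regression to the mean. It does not isolate the system under test. With 1:3 allocation the two within-arm tests also differ greatly in power for the same change, so one significant and one non-significant result is a likely outcome even when the arms behave identically.
2. Baseline values are collected in both arms, yet no stated analysis uses them as a covariate. An end-of-intervention t-test, on its natural reading, ignores them. The mixed model treats baseline as a response and estimates a separate baseline mean in each arm, which costs precision.
3. With no analysis marked as decisive, the choice could be made after the results are seen.

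At stake are precision that costs nothing to obtain, and a report in which improvement within an arm is read as evidence of effectiveness.

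**Working it through.** **The plan's own figure.** The inputs are "The sample size evaluated by significance level *p* = 0.05" and "80% power, 25% prevalence (controlled diabetes) and odds ratio 2", allocation 1:3, and the 15% loss allowance ("Because in RCT studies lost to follow up is approximately 15.0", in per cent). An odds ratio of 2 on 25% gives odds 2 × 0.25/0.75 = 0.667, that is 40%. The pooled rate is (0.40 + 3 × 0.25)/4 = 0.2875. Two-sided, with the simple pooled-variance formula:

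n(intervention) = (1.96 + 0.8416)² × 0.2875 × 0.7125 × 4 / (3 × 0.15²) = 95.28

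Multiplying by 1.15 gives 109.6 and 328.7, hence 110 + 329 = 439. The figure reproduces. It is sized on a binary control rate, so it neither supports nor refutes the points below; it supplies only the arm sizes.

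**Within-arm tests.** Suppose both arms truly change by the same 0.2 SD of change (assumption). The noncentrality is 0.2 × √n: 2.10 for n = 110 and 3.63 for n = 329. Two-sided 5% one-sample t-tests then have power 0.547 and 0.951.

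- P(disagree) = 0.547 × 0.049 + 0.951 × 0.453 = 0.027 + 0.431 = about 0.46.
- In about 43% of trials only the control arm is significant, with no difference between arms.
- Other common changes: 0.10 SD gives 18% and 44% power and 46% disagreement; 0.15 SD gives 35%, 77% and 59%; 0.30 SD gives 88%, almost 100% and 12%.
- After 15% loss (94 and 280 patients), 0.2 SD gives 48%, 92% and 51%.

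**Precision of the between-arm analyses.** Let r be the baseline to month-6 correlation. The article does not give it, so 0.3 to 0.8 is an assumed range. With equal variances at both times and independent patients, the relative variance of the estimated effect is:

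- unadjusted month-6 t-test: 1
- two-period Group by Period term (change score): 2(1 − r)
- baseline adjustment: 1 − r²

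The ratio of the last to the second is (1 + r)/2, so the saving is (1 − r)/2 against the interaction and r² against the t-test. The detectable difference at 80% power for the t-test is 2.8016 × √(1/110 + 1/329) = 0.309 SD; the others follow by multiplying by the square root of the relative variance.

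| r | Interaction variance | Adjusted variance | Saving vs interaction | Saving vs t-test | Detectable difference in SD: t-test / interaction / adjusted |
|---|---|---|---|---|---|
| 0.3 | 1.40 | 0.91 | 35% | 9% | 0.309 / 0.365 / 0.294 |
| 0.5 | 1.00 | 0.75 | 25% | 25% | 0.309 / 0.309 / 0.267 |
| 0.7 | 0.60 | 0.51 | 15% | 49% | 0.309 / 0.239 / 0.220 |
| 0.8 | 0.40 | 0.36 | 10% | 64% | 0.309 / 0.195 / 0.185 |

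Below r = 0.5 the interaction is less precise than the unadjusted t-test. A fit to one simulated complete data set (110/329, r = 0.6) confirmed that the stated interaction equals the change-score difference exactly (estimate −0.335, SE 0.1003 for both). The SE was 0.0872 with baseline adjustment and 0.1067 for the month-6 t-test.

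**Cost of leaving the choice open.** If the t-tests are also run on a primary outcome and either the t-test or the interaction may count, simulation under no effect (r = 0.5 and 0.7) puts the error rate per outcome at about 9% instead of 5%.

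**Patients without a month-6 value.** At 15% loss, 0.85 × 110 ≈ 94 and 0.85 × 329 ≈ 280 remain. That is 374 of 439, leaving about 65 with no month-6 measurement.

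**The case against.** The strongest reply is that the mixed model is the only procedure tied by name to the primary outcomes, is a valid between-arm contrast, and uses baseline. Measures already defines effectiveness by comparing the groups, so nobody proposes to compare within-arm p-values. The precision gain hangs on an assumed correlation and falls to 10% at r = 0.8.

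Most of that is fair, and it limits what can be claimed. Several stronger readings are tempting but not supported:

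- *The t-tests break intention-to-treat.* A t-test by randomised arm does not do so in itself. It would conflict with including all individuals' data only if missing month-6 values were left unfilled. The article is silent on this, and such handling may sit in a plan that is not shown. Month-6 ANCOVA would lose the same patients.
- *Each outcome is tested three times.* The outcomes for the t-tests are not named, so this is an inference.
- *The model's first period is a routine value up to six months old.* Screening does accept such values, and the wording shifts between enrollment and baseline. But Follow-up speaks of month 0, Measures says HbA1c and fasting glucose are determined for each patient taken into the groups, and the schedule in Table 3 is not visible. The term is loose; stale values are not established.
- *All patients were selected on high glucose.* Table 1 also admits people already diagnosed, so regression to the mean applies to an unknown share.

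Two points remain after all this. The text does not say which analysis decides, and within-arm tests cannot show a treatment effect however they are labelled.

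**Conclusion.** The point holds in this limited form and should be acted on. The article fixes overlapping analyses without ranking them. It includes uncontrolled tests that do not answer its own between-group question, and no stated analysis is the efficient use of the baseline.

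The within-arm figures (55% and 95% power, 46% disagreement) rest on a chosen common change of 0.2 SD of change. Disagreement runs from 12% to 59% for changes of 0.1 to 0.3 SD with the full arms. The variance savings rest on r between 0.3 and 0.8, on equal variances and on independent patients. Baseline adjustment has the lowest variance throughout that range. The planned interaction is a sound analysis whose fault is lost precision, not bias, and it is compatible with the intention-to-treat statement. How patients are grouped under physicians is a separate matter and is not part of this point.

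**What to change.** In Statistical analysis, Stage 2:

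1. For each primary outcome, name one primary between-arm analysis that adjusts for the month-0 value. The preferred form is a mixed model with the arms' month-0 means constrained equal, including every randomised patient with any value. Month-3 HbA1c may be added where collected. The effect is the group difference at month 6.
2. Call the first period month 0 instead of enrollment, in line with Follow-up.
3. Report within-arm changes as descriptive summaries, without tests offered as evidence of effect.
4. Drop the unadjusted t-tests as evidence of effect on the primary outcomes, and say which outcomes any remaining t-tests serve.
5. If month-6 ANCOVA or t-tests are kept, state how the missing month-6 values (about 65 of 439 at 15% loss) are handled so that the statement about including everyone's data holds.

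The cost is wording only. No new patients, visits or samples are needed.

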## Discussion

This study describes the first comprehensive clinical decision support system intended for diabetes screening, diagnosis, treatment and monitoring in Turkey. Moreover, this clinical decision support and monitoring system using evidence-based guidelines will pave the path for other medical specialties providing health services to diabetes patients. In addition, remote monitoring of patient data and alert mechanisms are also implemented in this study. Patient adherence to treatment in medication and lifestyle changes will be provided.

Using CDSMS based on current diabetes guidelines and telemonitoring systems will provide patients a means to receive effective treatment and regular monitoring. This will reduce possible complications, hospitalization, morbidity, and mortality caused by diabetes while also reducing the cost of treatment.

Electronically monitoring period screenings will provide early diagnosis and protection from potential diseases. This will enable patients to live longer and healthier lives, reduce treatment costs, and prevent the labor loss.

In CDSMS, patients actively participate in their treatment by regularly inputting measurement values and receiving motivational and reminder messages. Constant communication will increase the patient’s self-efficacy, thereby reducing emotional stress and increasing the patient quality of life.

Information technologies are integrated to patient care and monitoring in primary health care services with the proposed CDSMS based on predictive modeling. This new comprehensive and integrated approach will contribute to rapidly evolving e-health technology in the world using national information and technology savings. In addition, patient data will be collected when using rule based CDSMS. As a future study, an intelligent clinical decision support system will be developed using machine learning and artificial intelligence technologies on collected data.

## Abbreviations

CDSMS: Clinical decision support and monitoring system
DM: Diabetes Mellitus
RCT: Randomized controlled trial
